### Credibility of Treatment Rating Scale

We will use the Credibility of Treatment Rating Scale to assess, from the participants’ viewpoint, the credibility of the acupuncture treatments [26, 27]. This scale has four items: (1) the perceived logic of the treatment, (2) whether they would recommend the treatment to their friends who have similar complaints, (3) whether they believe that the treatment will alleviate their complaint, and (4) whether they believe that the treatment will alleviate other complaints.

### Blinding success assessment

Once the final treatment has been completed, we will test the success of blinding by asking the participants the following question: “When you volunteered for the study, you were informed that you had equal odds of receiving traditional electroacupuncture or electroacupuncture-like treatment. Now that our study is complete, which type of treatment do you think you received?” Three choices will be provided for participants: EA group, SEA group, and uncertain. If participants do not choose “uncertain,” we will ask them why they made their choice [3].

### Monitoring

To ensure the quality of this trial, the whole process will be supervised by a qualified clinical trial expert. The trial will be carried out by Shanghai Municipal Hospital of Traditional Chinese Medicine. The Clinical Research Center for Drugs of the Shanghai University of Traditional Chinese Medicine will monitor the data, including interim results. If any problems are identified, the center may decide to change this protocol. Any such changes will be announced to all persons involved in the trial in writing after they have been approved by the relevant ethics committee. In addition, a qualified clinical trial expert will monitor this study. The principal investigator will take full responsibility for the conduct of the trial and will make the final decision on any changes required.

### Data management

The clinical trial management platform ResMan will be used to manage the original data, which will be collected by blinded assessors and double-entered. The data management system will be tested beforehand, and relevant users will be trained on it before it is officially launched. The database will be protected by passwords. The original data for a participant will be entered within 1 week after their discharge from hospital. If there are issues with the data, the data supervisor will request clarification from a researcher. The clinical supervisor will monitor the work of the clinical trial center at least once a month.

### Statistical analysis

An independent statistician blinded to group allocation will perform the statistical analyses using the statistical software SPSS 23.0 for Windows. The analyses will include an intention-to-treat analysis incorporating data from any participants who have dropped out of the trial. We will use multiple imputation for missing data. All demographic and clinical characteristics of the subjects (such as sex, age, and weight) will be analyzed using descriptive statistics. We will identify the homogeneity of demographic characteristics and study variables between the two groups. Continuous variables will be reported as means ± standard deviations whereas qualitative data will be presented as frequencies and percentages. To analyze the primary outcome, the area under the curve of the NRS pain scores will be calculated using the trapezoidal method. Comparisons between groups will be made using Student’s *t*-test. The secondary outcomes—BP, HR, QoR-15, SF-36, and actigraphy assessments (total sleep time, sleep awakenings, and sleep efficiency)—will be compared between the two groups with Student’s *t*-test or the Wilcoxon rank-sum test. All reported *p* values will be two-sided, and *p* < 0.05 is considered statistically significant.

## Discussion

Postoperative pain is common after nasal endoscopic surgery. It can interfere with the quality of sleep and delay postoperative recovery. It is also a significant burden on individuals. We chose to study acupuncture because previous studies have shown that it is an effective and safe method of pain management [11, 28–30]. If postoperative pain is not treated immediately, patients can develop long-term chronic pain. However, EA specifically for the relief of postoperative pain after nasal endoscopic surgery has not yet been studied through a RCT.

This study will be conducted at the Shanghai Municipal Hospital of Traditional Chinese Medicine. Acupuncture has already been used for inpatients. However, it has not been used for immediate analgesia for a surgical patient. This study is designed to investigate the efficacy and safety of acupuncture as an adjunctive therapy for relieving postoperative pain and discomfort. If this study confirms that acupuncture is effective and safe, acupuncture could be implemented as a new standard for relieving postoperative pain in Chinese and Western medicine.

There are several challenges and limitations in this study. Firstly, patients with different types of nasal disease will be screened to reduce variability within the study population. Therefore, only participants who need nasal endoscopic surgery for sinusitis due to nasal polyps will be included. In addition, randomization will be done rigorously so that the number of participants in the two groups is balanced. Secondly, the preoperative EA or SEA treatment must be carried out in the recovery ward within 2 h before the operation. We found many studies in which the acupuncture was performed before the induction of anesthesia in the operating theater [6, 31, 32]. However, the surgical team were concerned that this would lengthen the pre-surgical preparation time. Therefore, the timing of the preoperative treatment may not be ideal. Thirdly, it is difficult to schedule the acupuncture treatment because the surgery time is uncertain. An acupuncturist must wait until the surgery has ended so that they can immediately perform the postoperative treatment. Fourthly, because of the nature of clinical trials of acupuncture, it is inevitable that the acupuncturist is aware of treatment allocation. However, the acupuncturists will not be involved in assessing patients or the analysis. To prevent an acupuncturist from accidentally revealing the group allocation, their interactions with the patients will be limited. All patients will wear an eye mask while receiving treatment, which will occur in a private area. Overall, blinding will be strictly enforced.

Though there are many difficulties, we will strive to standardize the steps of the study to ensure its quality. We hope this pilot RCT will provide clinical evidence for the feasibility of EA in alleviating postoperative pain. The outcomes will inform the design of a further full-scale trial.

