## Background

Postoperative pain is an important symptom following nasal endoscopic surgery for sinusitis due to nasal polyps. Effective management of postoperative pain after nasal endoscopic surgery is especially important for patient recovery. Pain due to a nasal filling may interfere with breathing, sleep quality, and patient satisfaction. According to previous reports, a failure to treat acute pain immediately may cause long-term chronic pain [1, 2]. The effective relief of acute pain is a challenge for patients and physicians following nasal endoscopy. Analgesic drugs, especially opioid analgesics, are often used to relieve pain after surgery. However, there are risks due to side effects, such as respiratory depression and drowsiness, which can lead to a delayed postoperative recovery. Thus, a safe and effective way to control postoperative pain and reduce recovery times needs to be identified.

Acupuncture has been widely used for pain relief, and its analgesic effects have been reported worldwide. Several studies have shown that acupuncture can relieve pain after surgery, including oral surgery [3, 4], cardiac surgery [5], laparoscopic cholecystectomy [6–8], gynecological surgery [9, 10], back surgery [11], and nasal surgery [12]. Therefore, acupuncture may relieve postoperative pain following nasal endoscopic surgery. Despite the positive results of these previously published studies, the results are not dependable due to issues such as small sample sizes, inadequate randomization, and lack of blinding. Therefore, high-quality evidence is needed to confirm the previous findings and for a protocol to be developed for the use of acupuncture for postoperative pain.

For those reasons, we designed a randomized controlled trial (RCT) using appropriate randomization, rigorous concealment of allocation, and blinding to examine the efficacy of electroacupuncture (EA) in relieving postoperative pain after nasal endoscopy. We aim to determine: (1) whether EA is useful for relieving postoperative pain after nasal endoscopy and (2) whether it can reduce postoperative recovery times. This study may provide high-quality evidence to support a standard protocol for the clinical application of EA for treating postoperative pain after nasal endoscopic surgery.

We hypothesize that EA is effective, safe, and feasible for postoperative pain management after nasal endoscopic surgery.

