### Sample size

This is a pilot study. In the relevant literature, there are no previous studies utilizing the same evaluation method as the primary outcome to compare a sham acupuncture control. Therefore, we were unable to calculate the statistical power formally. The appropriate sample size for a two-arm pilot study should be more than 12. We assumed a 20% dropout rate, so that we will recruit 15 participants into each group. We will, therefore, recruit a total of 30 individuals for this RCT [13–15].

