### Randomization and allocation concealment

A random sequence will be produced by block randomization using the software SPSS version 23.0 by an independent research assistant. After the participants have completed the screening process and baseline assessment, they will be randomly assigned to one of the groups in a 1:1 ratio using random numbers in opaque envelopes. The treatment allocation codes will not be revealed before the first treatment. In an effort to minimize breaks in coding, the principal investigator who designed the trial and the research personnel who perform the outcome assessments will also be blinded to the treatment assignment.

Before the beginning of treatment, we will tell the participants that they have the same probability of being assigned to the EA group or the SEA group. To ensure that participants remain blinded, they will wear an eye mask during treatment. Only the acupuncturist who performs the treatment will know the group allocation at the time of treatment. The principal investigator, the data analysts, the outcome assessors, and statistician will remain blinded.

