### Intervention protocol

All participants will be asked to fast from 8 h before the operation. They will undergo a standard operative procedure and receive postoperative treatment. Participants will be transferred to the ward within 30 min after the operation. EA or SEA will be given within 2 h prior to the surgery, immediately after surgery on arrival in the recovery ward, and daily following surgery for 3 days (five treatment sessions in total). If a participant drops out before completing the study, the reason will be recorded.

The acupuncture methods are described in Table 2. In each treatment session, the patients will be in a private area and placed in the supine position. They will wear an eye mask to prevent them from observing the treatment procedure. The researcher will sterilize the patient’s skin with 75% alcohol wipes before treatment. Each treatment session will last for 30 min. When the needles are removed, the researcher will use a clean piece of cotton wool to prevent bleeding by compressing the points. In the first treatment, 11 acupoints will be used and 17 acupoints will be used in the subsequent postoperative treatments. The acupoints and rationale are summarized in Table 3.

**Table 2 Tab2:** Treatment methods of electroacupuncture and acupoints

	EA group	SEA group
Acupoints	All sessions: LI4, PC6, HT7, LI20, ST36, GV23 Postoperatively: GV20, GV29, EX-HN22, SP6	All sessions: LI4, PC6, HT7, LI20, ST36, GV23 Postoperatively: GV20, GV29, EX-HN22, SP6
Depth of insertion	10 mm: HT7, GV20, GV23, GV29, LI4, LR3	No insertion
	30 mm: LI20, SP6, PC6, ST36	
Needle type	Steel needles (Wuxi Jiajian Medical Co. Ltd. Wuxi, China)	Blunt needles (Streitberger placebo needle)
Needle sensation	With *de-qi* sensation	Without *de-qi* sensation
Electric stimulation	Three pairs of needles: LI4–ST36 (bilaterally), GV20–GV23 Connected to an electric stimulator (HANS-200B) Deliver continuous wave-type mid-frequency (15Hz) current of 2 mA	Three pairs of needles: LI4–ST36 (bilaterally), GV20–GV23 Connected to an electric stimulator (HANS-200B) No electrical current delivered

*EA* electroacupuncture, *SEA* sham electroacupuncture

**Table 3 Tab3:** Acupoint selection and rationale based on traditional Chinese medicine

Acupoint	Location	Traditional Chinese medicine indication	Suggested technique

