### Outcome measures

The participant’s recovery will be monitored during and after the operation. The primary outcome is postoperative pain scores measured using a NRS. The secondary outcomes include heart rate (HR) and blood pressure (BP) after the operation, sleep quality during the hospital stay (actigraphy), quality of recovery, and overall health. In addition, the exact type of operation and when EA or SEA treatment is given will be recorded for analysis. If the participants cannot be managed according to the protocol for any reason, including side effects, no further data will be collected. The assessment schedule is detailed in Table 1.

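### The primary t-test on the NRS AUC uses neither the operation type that the protocol records for analysis nor the nasal packing that it names as a source of pain

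*Protocol article*

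**What the plan says.** All places are in the protocol article.

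- **Discussion:** "patients with different types of nasal disease will be screened to reduce variability within the study population". Only patients with sinusitis due to nasal polyps are admitted. The inclusion criteria set no limit on extent or type of operation or on packing.
- **Background:** "Pain due to a nasal filling may interfere with breathing, sleep quality, and patient satisfaction".
- **Intervention protocol:** "They will undergo a standard operative procedure and receive postoperative treatment". The procedure is not described further, and packing is not mentioned.
- **Outcome measures:** "the exact type of operation and when EA or SEA treatment is given will be recorded for analysis".
- **Randomization and allocation concealment:** "A random sequence will be produced by block randomization using the software SPSS version 23.0". No stratification factor is named. The Discussion adds that "randomization will be done rigorously so that the number of participants in the two groups is balanced", which concerns group sizes.
- **Statistical analysis:** the AUC of the NRS scores is compared between groups with Student's t-test. No covariate is named.

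**The concern.** The protocol treats the operation as something that can differ between patients and is worth analysing, and it names packing as a cause of the pain that it measures. The one analysis that it fixes for that pain cannot take in either. A two-sample t-test has no place for a covariate, so recording the operation for analysis has no stated effect on the primary result. Table 1 schedules no NRS score before surgery, so no baseline pain score is available to absorb part of the between-patient variation.

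Two things are at stake in a trial of 30. First, variation due to the operation stays in the error term and widens the confidence interval. Second, if the arms happen to differ in surgical mix, the observed EA-minus-sham difference is shifted by that mix, and an adjustment chosen after seeing the data would be hard to defend. The trial is meant to inform a full-scale trial, so both its estimate and its SD may be reused.

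The statements on a standard procedure and on recording the exact type also sit uneasily together. If the procedure is the same for all, there is little to record. If the type varies, the reader needs to know what is standard.

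**Working it through.** **1. The plan's own figure.** The Sample size section says "The appropriate sample size for a two-arm pilot study should be more than 12" and assumes 20% dropout. Read as 12 per arm, 12 / (1 − 0.20) = 15 per arm, 30 in total. This matches the plan.

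**2. Assumptions, none from the documents.** One two-level surgical or packing factor, carried by 30% or 50% of patients (9 or 15 of 30), shifts the AUC by g = 0.5, 1.0 or 1.5 within-level SDs. The factor is unrelated to the block structure.

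**3. How often the arms differ.** With K carriers among 30 and 15 per arm, the number x in the EA arm is hypergeometric and the arms differ by |2x − K| patients.

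- K = 15: P(difference ≥ 3) = 1 − 2·C(15,7)·C(15,8)/C(30,15) = 1 − 2 × 6435² / 155,117,520 = 0.466.
- K = 9: 1 − 2·C(9,4)·C(21,11)/C(30,15) = 1 − 2 × 126 × 352,716 / 155,117,520 = 0.427.
- P(difference ≥ 5), or 33 percentage points: 0.143 (K = 15) and 0.109 (K = 9).

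These figures depend on K being odd, since the difference is then odd. For an even K, a difference of at least 3 means at least 4:

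- K = 14: 1 − [C(14,7)·C(16,8) + 2·C(14,6)·C(16,9)]/C(30,15) = 1 − (44,169,840 + 68,708,640)/155,117,520 = 0.272.
- K = 10: 0.245 by the same formula.

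Averaging over a binomial K gives 0.318 at 30% and 0.362 at 50%. So an imbalance of 3 or more arises in roughly a quarter to just under half of randomizations, depending on the exact count.

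**4. Loss of precision.** SD without the factor relative to SD with it = √(1 + g²·p·(1 − p)).

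| g | p = 0.3 | p = 0.5 |
|---|---|---|
| 0.5 | √1.0525 = 1.026 | √1.0625 = 1.031 |
| 1.0 | √1.21 = 1.100 | √1.25 = 1.118 |
| 1.5 | √1.4725 = 1.213 | √1.5625 = 1.250 |

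**5. Error rates with no EA effect** (simulation, 60,000 trials per scenario, K = 9 or 15).

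- Over all randomizations: t-test 4.9% to 5.2%; ANCOVA 4.9% to 5.1%.
- Only trials whose arms differ by at least 5 patients: the mean shift is about 0.18, 0.35 and 0.53 SD for g = 0.5, 1.0 and 1.5. The t-test rejects in about 7%, 12% and 17–18%; ANCOVA in 4.7% to 5.2%.

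**6. The same thing in NRS points.** If half the patients carry a factor worth 2 points, the chance difference in proportion has SD √(0.5 × 0.5 × 2/15) = 0.183, and the resulting difference in means has SD 0.183 × 2 = 0.365, a 95% range of about ±0.72. A factor worth 1 point gives about ±0.36. But such a factor has within-arm SD 2 × √0.25 = 1 point, and its contribution to the standard error is √(2 × 1²/15) = 0.365, the same number. This is sampling error that the t-test already counts.

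**The case against.** The strongest reply has four parts.

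- **The Discussion claims only a reduction in variability.** Excluding other nasal diseases does reduce it. A reader might infer that the claimed reduction is not achieved; the text does not support that, and the sentence need not be removed. This part stands in full.
- **Variation in surgery and packing is largely inferred.** The protocol promises a standard procedure and nowhere says that some patients are packed and others not. The Background remark on nasal filling is general. This stands for packing. It stands only partly for the operation, since recording its exact type for analysis presupposes that it can vary.
- **Chance imbalance is not bias in the test.** A reader might infer an inflated false-positive rate. Steps 5 and 6 show otherwise: over randomizations the unadjusted test is valid. This stands, and limits the point to precision and to what happens once an imbalance has occurred.
- **Covariates belong in the SAP, which is not shown, and unstratified blocks are legitimate in a small pilot.** A reader might infer that the operation type will never be used, but the stated intention to record it for analysis, and the planned comparison of study variables between the groups, speak against that. Stratification is a choice, and its absence is no error. What survives is narrower: the protocol does fix the primary test, and that test leaves out a variable which the protocol itself collects for analysis.

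**Conclusion.** The point holds in limited form. The protocol records operation type for analysis and names packing as a source of pain, and then fixes a primary test that uses neither. The test remains valid at 5%. The cost is an SD about 3% larger if the factor matters little (0.5 SD) and up to 25% larger if it matters a great deal (1.5 SD at 50% prevalence), together with an estimate shifted by about 0.2 to 0.5 SD in the minority of trials with a large imbalance (11% to 14% when exactly 9 or 15 patients carry the factor, fewer for even counts).

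Prevalence and effect size are assumptions throughout; the documents give neither. If nearly all patients have the same operation and the same packing, the loss is close to nil. It is a modest improvement to a pilot, worth making because it costs almost nothing.

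**What to change.** 1. At baseline, before the envelope is opened, record the planned operation and whether packing is planned. The planned operation is the right covariate because the first EA or sham session comes before surgery, so the operation actually performed is known only after randomization and treatment have begun.
2. In the Statistical analysis section, make the primary comparison a linear model (ANCOVA) of the NRS AUC on treatment and one two-level planned-operation factor, with the levels defined before the first patient is randomized. Keep the unadjusted t-test as a sensitivity analysis.
3. Report operation type and packing by arm.
4. Reconcile the Intervention protocol and Outcome measures sections on whether the operation is standard or varies.

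The cost is one baseline field and one degree of freedom (30 − 3 = 27 instead of 30 − 2 = 28). There is little gain if almost everyone falls in one level, and packing that varies independently of the planned operation stays unadjusted, though it becomes visible. Stratifying the blocks by the same factor is optional; with 30 patients it risks an incomplete block in each stratum.

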### Trial status

The first investigators’ meeting took place on 31 May 2019. The RCT is in preparation now and will launch on 1 May 2020. Recruitment is expected to end in late 2020.

## Data Availability

The trial results will be published in peer-reviewed scientific papers and in posters or oral presentations in conferences. All data and the protocol will be available 3 months after our publication of the results for a period of 3 years. The trial data will be available from the corresponding author upon reasonable request.

## Abbreviations

BP: Blood pressure
EA: Electroacupuncture
HIV: Human immunodeficiency virus
HR: Heart rate
NRS: Numerical rating scale
QoR-15: 15-item Quality of Recovery Scale
RCT: Randomized controlled trial
SEA: Sham electroacupuncture
SF-36: 36-item Short Form Health Survey
